### Surgeon experience and type of plates

Our previous retrospective follow-up study concluded, that neither surgeon experience nor type of volar locking plate was associated with the complication rate [3]. Therefore, we consider surgeon experience and type of plate of no to minor clinical importance for the outcomes of this study. Hence, all physicians that usually treat DRF conservatively and operatively at our hospital will treat patients. No selection, nor restrictions regarding treating physician and fracture type will be imposed and operating physicians range from residents to consultants.

### Statistical plan and analysis

#### Sample size

The sample size was calculated based on a 20% difference in complication rate between the two treatment groups, an alpha level of 5% and a power of 80%. Consequently, each group shall at least consist of 49 participants. The control group was decided to be of equal size.

#### Data management

All data will be managed in accordance with Good Clinical Practice. Papers containing patient identifiable data along with informed consent are physically stored in a locked room. Study data will be collected and managed using REDCap electronic data capture tools hosted at Aarhus University, Denmark [25]. The Data Steering Committee (RT, [name], JP) will review included and excluded patients every 14th day. If patients do not show up for follow-up in the outpatient clinic, The Data Steering Committee will contact the patient by phone and/or mail in order to ensure participant retention and complete follow-up. Only the Data Steering Committee will have access to the final trial data set. No publication of the data is planned; however data will be stored according to national legislation.

#### Statistical analysis plan

That data will be analyzed using Fisher’s exact test and Mann Whitney U test. The desired applied statistic is odds ratio with Pearson’s 95% confidence interval. Should any data be lost in the follow-up, the Last Observation Carried Forward concept will be used. Treatment arm 3 will be analyzed after 6 months follow-up and published separately.

All test will be two-tailed and assessed at the 5% alpha level. Categorical measures will be presented as percentages. An intention-to treat and per-protocol analysis will be considered. Continuous measures will be presented as means with standard deviations and medians with inter-quartile range. Treatment effects over time will be assessed using linear mixed effect models with patient treated as random factor. A normal distribution with an identity link function will be assumed for continuous measures, while a multinomial distribution and cumulative logit function will be applied to ordinal outcomes.

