Volar plating of DRF may harm patients. Complication rates of up to 33% have been reported in surgically treated DRF patients [10–14]. Our own estimation of the complication rate after volar plating of DRF is 14.6% [95% CI 11.8–17.7%] in a retrospective cohort of 595 patients with 3.2 years follow-up [3]. This high complication rate is not insignificant for the patients. Neurologic disturbances, tendon irritation and rupture, infection, etc. often lead either to a re-operation or an increase in out-patient visits and may result in permanent morbidity and impaired function [15].

Furthermore, volar plating improves the early functional recovery, but long-term functional results are similar with other treatment modalities in patients ≥65 years [16]. However, volar plating is still the gold standard in the treatment of DRF in adults regardless of age.

An increase in complications with no clinically significant difference between the functional outcome of operatively and conservatively treated patients was demonstrated [16, 17]. Furthermore, the patients treated operatively had a higher complications rate than the conservatively treated patients [17]. In addition, patients with DRF treated nonoperatively have shown to have less pain and better or equal wrist function after a 1 year follow-up than those treated surgically [18]. A Danish review of operatively treated patients suggest a more restrictive choice of treatment for DRF amongst the elderly than the NCG stipulate [2]. All things considered, no existing evidence proves the benefit of treating DRF operatively in the elderly.

Here, we question whether the potential benefit of volar plating, namely an earlier functional recovery outweighs the risk of encountering a complication. Especially in the light of retired patients (≥ 65 years), where return to work is not a burning issue, it seems worthwhile to investigate this issue both in the interest of the patients and society.

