#### Intervention group

Treatment arm 1:Open reduction and volar plate fixation utilizing Acu-Loc®, Acumed or Variax®, Stryker with a standard Henry approach to the distal radius and pronator quadratus repair if possible. The vast majority of patients will be operated in regional anesthesia and the remaining patients in general anesthesia. It is the choice of the surgeon whether a tourniquet will be used. After surgery the wrist is immobilized in a dorsal plaster cast for 2 weeks followed by further 3 weeks of immobilization with a removable orthosis. A single hand therapeutic instruction will take place.
Treatment arm 2:Conservative treatment consists of dorsal plaster cast immobilization for 5 weeks. Only discomfort, neurologic deficits or signs of infection warrant removal and replacement with another dorsal plaster cast. A single hand therapeutic instruction will take place.

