#### Primary outcomes

The complication rate will be estimated at day 0, 2 weeks, 5 weeks, 6 months, and 12 months after the injury.

Complications are defined as the presence of:Sensory disturbance, including carpal tunnel syndrome and chronic regional pain syndromeFlexor tendon rupture and irritationExtensor tendon rupture and irritationHardware failure, e.g. osteosynthesis looseningInfection: superficialInfection: deepReoperation with hardware replacementReoperation with hardware removal (partial or total), which is not routinely performed in DenmarkVascular compromised (capillary refill ≥2 s)

Patients will report complications at the given timepoints by answering a questionnaire stating either yes / no and a free-text explanation. If the patient states any complications, a member of the research group will qualify the answer and fill in the free text. However, a YES can only be qualified and shall never be erased if the physician does not agree with the patient’s opinion or explanation.

The Danish version of the Quick Disabilities of the Arm, Shoulder and Hand [22] will be used to assess the level of functionality prior to injury, after 2 weeks, 5 weeks, 6 months, and 12 months. The minimal clinically relevant difference is 16 to 20-point difference in Quick DASH [19–21].

Range of motion is measured by a registered nurse using a goniometer. To ensure the observer is blinded, the patient is instructed not to talk about the treatment. Furthermore, all wrists will be covered by a glove concealing potential scares (Fig. 3). The following data are thus collected in a blinded fashion wrist flexion, extension, pronation, supination, radial deviation, ulnar deviation. The contralateral side will serve as a reference and history of injuries or operations of the contralateral side will be recorded.

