#### Secondary outcomes

The patient reported outcome measure Quick DASH will be supported by the following secondary outcome measures:▪ A Danish version of the Patient rated Wrist Evaluation questionnaire (PRWE) will be evaluated after 6 month and 12 months [23].▪ Grip strength of both left and right hand will be estimated as the maximum and average of score of three repetitions of each hand with alternating hands between attempts after 6 months and 12 months using a dynamometer.▪ A pinch gauge where both left and right hand are evaluated (yes/no) if the participant can pinch a sheet of paper. This is collected after 6 months and 12 months by an unblinded physician or research year student.▪ The potential flexion deficit of the 1st finger towards the base of the 5th finger measured as the distance (cm) from the pulp of the 1st finger to the carpometacarpal joint of the 5th finger after 6 and 12 months.▪ The pulp-to-palm distance of the distal 2nd-5th finger and palmar surface of the side treated for DRF after 6 and 12 months.▪ The experienced pain during activity within the preceding 14 days before the injury and at 6- and 12-months follow-up stated on a 0–10 Numeric Rating Scale (NRS).▪ The pain at rest after 2 and 5 weeks given NRS.▪ EQ5D (European Quality of life – 5 Dimensions) after 6 months and 12 months. This is registered by an unblinded physician or research year student [24].▪ The self-reported use of pain medication at day 0, after 2 weeks, 5 weeks, 6 months, and 12 months.▪ The prescribed use of pain medication compared 12 months before with 3 and 12 months after the injury.▪ Standardized radiographs of the injured wrist at day 0 before and after closed reduction (all groups), week 2 (conservative treatment group, not reviewed before completion of the follow-up period), week 5 (all groups).

*The following baseline demographics* will be recorded: gender, age, side of DRF, hand dominance (right-handed, left-handed, ambidextrous), working status, American Society of Anesthesiologists Classification (ASA class 1–6), smoking (cigarettes/day), alcohol consumption (units/week) and diabetes (yes/no).

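### Last observation carried forward enters pre-injury or immobilisation-period scores, and early no-complication answers, as 12-month outcomes

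*Protocol article*

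**What the plan says.** The Statistical analysis plan section gives one rule for missing data: "Should any data be lost in the follow-up, the Last Observation Carried Forward concept will be used". It is not limited by endpoint, visit or analysis. It follows the naming of Fisher's exact test and the Mann-Whitney U test. The next paragraph adds that "Treatment effects over time will be assessed using linear mixed effect models with patient treated as random factor".

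The schedule decides what can be carried:

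- **Quick DASH** "will be used to assess the level of functionality prior to injury, after 2 weeks, 5 weeks, 6 months, and 12 months" (Primary outcomes).
- **Range of motion** is first measured at 5 weeks (Table 1).
- **PRWE** "will be evaluated after 6 month and 12 months" (Secondary outcomes). Grip, pinch and EQ5D also start at 6 months.
- **Complications**: "The complication rate will be estimated at day 0, 2 weeks, 5 weeks, 6 months, and 12 months after the injury". After a positive answer, "a YES can only be qualified and shall never be erased" (Primary outcomes).

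Under Interventions, the plated wrist is "immobilized in a dorsal plaster cast for 2 weeks followed by further 3 weeks of immobilization with a removable orthosis"; the conservative arm stays in a cast for 5 weeks. The Background expects that "volar plating improves the early functional recovery, but long-term functional results are similar".

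**The concern.** Carrying a value forward is defensible only if the outcome would have stayed about where it was last seen. Here it would not. Function falls at the injury, is still low at 2 and 5 weeks, and recovers afterwards. A score from that period, or from before the injury, does not estimate function at 12 months. Immobilisation also differs between the arms after week 2, and the article itself expects the early scores to differ and the late ones not to. The rule therefore places an expected transient difference in the comparison meant to show that late function is comparable.

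For complications, the rule is harmless after a YES but turns an early NO into a 12-month NO. Events that would have occurred after loss are counted as absent. Complication rate is the endpoint on which the trial is sized, and 50 allocated against 49 required leaves room for only 2% loss (1 − 49/50).

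In both cases the carried value is then analysed as if observed, so the stated precision is wrong as well.

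**Working it through.** **What is carried, by time of loss**

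| Endpoint | Lost before 2 weeks | Lost after 2 or 5 weeks | Lost after 6 months |
|---|---|---|---|
| Quick DASH | pre-injury score | immobilisation-period score | 6-month score |
| Range of motion | nothing | 5-week value, if that visit took place | 6-month value |
| PRWE, grip, pinch, EQ5D | nothing | nothing | 6-month value |
| Complication YES | correct | correct | correct |
| Complication NO | may be outdated | may be outdated | may be outdated |

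**Quick DASH.** The article gives neither a loss rate nor expected scores. Assume 5-week means of 35 (plate) and 45 (cast), a true 12-month mean of 10 in both arms, and loss of a share d after week 5.

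LOCF mean = (1 − d) × 10 + d × (5-week mean)

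- 10% in both arms: plate 9 + 3.5 = 12.5; cast 9 + 4.5 = 13.5; false difference 1.0.
- 5% plate, 15% cast: 9.5 + 1.75 = 11.25; 8.5 + 6.75 = 15.25; false difference 4.0 against cast.
- 10% plate, 20% cast: 12.5; 8 + 9 = 17.0; false difference 4.5 against cast.
- 15% plate, 5% cast: 8.5 + 5.25 = 13.75; 9.5 + 2.25 = 11.75; false difference 2.0 against plate.

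A wider assumed gap at 5 weeks (40 v 60, true 12-month mean 15) gives 17.5 v 19.5 at 10% equal loss and 20 v 24 at 20%: 2 and 4 false points. A pre-injury score of 5 carried in both arms creates no difference but improves both means, from 15 to 14.0 at 10% loss.

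**The plan's own sample size.** The Sample size section gives 49 per group for a 20-point difference, two-sided 5% alpha and 80% power, without the two rates. Assumed rates of 25% v 5% reproduce it:

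n = [1.96 √(2 × 0.15 × 0.85) + 0.842 √(0.25 × 0.75 + 0.05 × 0.95)]² / 0.20² = (0.990 + 0.408)² / 0.04 ≈ 48.8, so 49.

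The same approximation gives power 0.81 at 50 per arm. Fisher's exact test, which the plan names, has about 0.75 on the same rates; that is a separate matter.

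**Complications under LOCF.** Let f be the share of the lost patients' events already recorded before loss.

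Recorded rate = true rate × [1 − d(1 − f)]

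| d (both arms) | f | Plate v cast | Difference | Power at 50 per arm |
|---|---|---|---|---|
| 0 | – | 25% v 5% | 20.0 | 0.81 |
| 10% | 0.5 | 23.75% v 4.75% | 19.0 | 0.78 |
| 10% | 0 | 22.5% v 4.5% | 18.0 | 0.76 |
| 20% | 0 | 20% v 4% | 16.0 | 0.70 |

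Most of this fall in power comes from the loss itself: dropping the lost patients gives 0.77 at 45 per arm and 0.72 (0.715) at 40. What LOCF adds is the bias in the rates and their difference.

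**Unequal loss, f = 0.** With true rates of 20% in both arms, 5% loss in one and 15% in the other gives 19% v 17%, a false 2 points against the arm that is followed better. With the 36% v 14% quoted in the Discussion, 5% plate and 15% cast loss gives 34.2% v 11.9%, or 22.3 points instead of 22; the reverse gives 30.6% v 13.3%, or 17.3. The direction depends on which arm is lost.

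**The case against.** **The mixed model.** A reader might infer that LOCF contradicts the planned mixed model. The text does not go that far. The rule follows two tests that need one value per patient, and nothing says the mixed model is fitted to filled data. What stands is that the section leaves this open, although the model needs no filling.

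**Size.** Loss rates, scores and event timing are all assumed. The false Quick DASH differences of 1.0 to 4.5 points are well below the 16 to 20 points that the article calls relevant, and the larger figures need unequal loss, which no section forecasts. Under equal loss, both biases work against the trial's own hypothesis of fewer complications and comparable function with cast, so the rule does not manufacture the hoped-for result. All of this stands and limits the severity.

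**Late events in the plate arm.** It is tempting to say that the missed events fall mainly there. Hardware events can occur only after plating, but the article gives no timing of complications by arm, so the calculation applies the same f to both.

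**Later-starting endpoints.** It would be too strong to say that nothing can be carried for PRWE or grip: a 6-month value can be carried to 12 months. Only patients lost before 6 months have none.

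**Mitigation.** The Data management section provides review every 14 days and contact after missed visits. This may keep loss low, but it does not repair the rule for those who are lost.

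**Unseen SAP.** A separate plan might add sensitivity analyses, so their absence is not the point. The point is a rule that the article states for all lost data.

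**Conclusion.** The point holds as a should-fix. The stated rule, applied to this schedule, gives biased 12-month comparisons of Quick DASH, range of motion and any complication, and treats carried values as data.

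Under equal loss, the function bias runs against cast and the complication difference shrinks toward zero; under unequal loss either can go in either direction. On the assumptions shown, the effect is 1.0 to 4.5 Quick DASH points and, at 10% equal loss, 1 to 2 of the 20 percentage points on complications. It grows with loss, for which the article gives no figure.

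A reader might infer that LOCF would overturn the trial's conclusion. The documents do not support that: the illustrated Quick DASH bias is a fraction of the relevant difference, and most of the complication difference survives.

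**What to change.** Delete the LOCF sentence and replace it with a rule for each type of endpoint.

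- **Quick DASH and range of motion:** estimate the 12-month treatment contrast, with its 95% confidence interval, from the mixed model already planned. Fit it to all observed visits with treatment, visit and treatment by visit, and state that no values are filled in. This assumes that loss is explained by the data observed, which is weaker than assuming that scores stay constant.
- **Any complication by 12 months:** keep every reported YES. For patients lost without an event, use multiple imputation, or cumulative incidence of a first complication with censoring at loss. The second assumes uninformative loss, and events are dated only to the visit, so say which is primary.
- **Sensitivity:** add a best/worst-case analysis for unknown complication status. With 5 of 50 patients unknown in each arm, the two extremes are 20 percentage points apart, so it belongs as a bound and not as the main result.
- **PRWE, grip, pinch and EQ5D:** analyse observed values and report how many patients have none.

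The Mann-Whitney and Fisher tests need not be dropped for this reason; state which data they use. The cost is a little more analysis work and slightly wider, more honest intervals, with no extra data. The change should be dated before any comparison by arm is seen.

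### Read plainly, the planned mixed model gives the arm difference one standard error at every visit; if Quick DASH spread differs between visits, single-visit intervals and tests are miscalibrated, in a direction the protocol cannot settle

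*Protocol article*

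**What the plan says.** The Statistical analysis plan section of the protocol article states the longitudinal model in two sentences: "Treatment effects over time will be assessed using linear mixed effect models with patient treated as random factor", and "A normal distribution with an identity link function will be assumed for continuous measures". It gives no residual covariance structure. It does not say whether arm-by-visit terms are fitted, or whether the pre-injury score is a response or a covariate.

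The same section sets the level of testing, "All test will be two-tailed and assessed at the 5% alpha level", and the handling of dropout, "Should any data be lost in the follow-up, the Last Observation Carried Forward concept will be used". It also names Fisher's exact test and the Mann-Whitney U test.

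Under Primary outcomes, Quick DASH serves to "assess the level of functionality prior to injury, after 2 weeks, 5 weeks, 6 months, and 12 months". Table 1 lists range of motion at 5 weeks, 6 months and 12 months. PRWE and grip strength are collected only at 6 and 12 months.

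The 2- and 5-week visits fall in or at the end of immobilisation. In arm 2, "Conservative treatment consists of dorsal plaster cast immobilization for 5 weeks"; arm 1 has 2 weeks of cast and then 3 weeks of orthosis.

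**The concern.** A single random patient effect with one residual variance forces the same total variance on every visit and the same correlation on every pair of visits. The Quick DASH schedule runs from the uninjured state through immobilisation to recovery, and there is little reason to expect equal spread across those states. Where the spread differs, the model borrows the average variance for every visit. An interval is too narrow at a visit with above-average spread and too wide at one with below-average spread.

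This matters because the trial's functional questions concern particular times. The Background sets earlier recovery after plating against the risk of complications, and the Research hypothesis expects function to be comparable. Quick DASH is among the primary measures in the abstract and under Primary outcomes, although Table 1 and the Research hypothesis place it with the secondary ones. If these time-specific contrasts are read from the mixed model, their nominal 5% level cannot be relied on.

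**Working it through.** **Inputs from the article.** Five Quick DASH visits; 50 patients per randomised arm (abstract and Randomization section); two-sided 5% level; relevant difference 16 to 20 points. The article gives no numerical result for this model, so there is no figure of its own to reproduce. The sample size rests on complications and supplies only n.

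**Inputs assumed.** Quick DASH SDs at each visit, since the article gives none. Visits are taken as balanced; carrying the last observation forward would keep them close to that.

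**Formulas.** For a random-intercept model with one residual variance, arm-by-visit means and balanced visits:

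- model SE at every visit = sqrt(2 × mean of SD_t² / n)
- true SE at visit t = sqrt(2 × SD_t² / n)
- type I error at visit t = 2 × [1 − Φ(1.96 × pooled SD / SD_t)], where pooled SD = sqrt(mean of SD_t²)

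With n = 50, sqrt(2/50) = 0.2.

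**Worked example, SDs 10/18/18/15/12.** Mean variance = (100 + 324 + 324 + 225 + 144)/5 = 223.4, so pooled SD = 14.95 and model SE = 14.95 × 0.2 = 2.99 at every visit.

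- 2 and 5 weeks: true SE 18 × 0.2 = 3.6; ratio 14.95/18 = 0.830; type I error 10.4%. Half-width 5.86 against a correct 7.06, so 1.2 points too narrow.
- 12 months: true SE 12 × 0.2 = 2.4; ratio 14.95/12 = 1.246; type I error 1.5%. Half-width 5.86 against 4.70, so 1.2 points too wide.

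Simulating 600 trials with no effect and fitting the model by REML gave a model SE of 2.98 at every visit, with type I errors of 10.7% and 12.0% at 2 and 5 weeks and 1.3% at 12 months. This agrees with the formula.

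**Other assumed patterns, by the same formula.**

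| SDs pre / 2 wk / 5 wk / 6 mo / 12 mo | Pooled SD | Type I, 2 wk | Type I, 5 wk | Type I, 12 mo |
|---|---|---|---|---|
| 12/16/16/14/13 | 14.29 | 8.0% | 8.0% | 3.1% |
| 10/18/18/15/12 | 14.95 | 10.4% | 10.4% | 1.5% |
| 8/20/20/15/10 | 15.42 | 13.1% | 13.1% | 0.3% |
| 8/18/18/18/18 | 16.49 | 7.3% | 7.3% | 7.3% |
| 8/16/18/20/20 | 16.99 | 3.7% | 6.4% | 9.6% |
| 18 throughout | 18.00 | 5% | 5% | 5% |

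The first three rows share one shape, high during immobilisation and low at 12 months. The fourth and fifth do not, and there the 12-month interval is too narrow. A second simulation (200 trials, between-visit correlation 0.5) of 8/16/18/20/20 gave a model SE of 3.40 at all five visits, while the true SEs ran from 1.6 to 4.0.

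**Pre-injury score as a covariate.** Only four visits are then pooled. If the remaining SDs are 20/20/17/15, pooled SD = 18.12 and type I error is 7.6% at 2 and 5 weeks and 1.8% at 12 months. With equal SDs it is 5% throughout.

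**Size on the score scale.** In the unequal patterns above, the half-width errors at 2 weeks, 5 weeks and 12 months run from about 0.4 points (6.66 against 6.27 at 2 weeks, fifth row) to 1.8 points (6.04 against 7.84 at 2 and 5 weeks, third row). The one exception is 12 months in the third row, 6.04 against 3.92, or 2.1 points. At 6 months the error is in some patterns close to zero.

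**The case against.** The strongest reply is that the flaw is read into the text. The article does not say that patient is the only random term, and it does not exclude visit-specific residual variances. Residual covariance is a detail that an article often leaves to a fuller plan, which is not shown here. This stands as a limit: the point is conditional on the plain reading. It does not remove the point, because the section does name the model class, the random effect, the distribution and the link, and standard software fits a homoscedastic random intercept from that description.

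A reader might go further and infer that intervals are too narrow during the cast period and too wide at 12 months. The documents do not support that. No section gives a Quick DASH SD at any visit, and none says that pre-injury scores sit near the floor. The direction at 12 months depends on whether the 12-month SD is below or above the pooled value, and a low pre-injury spread pulls the pooled value down. Last observation carried forward could also raise the 12-month spread by placing early scores there.

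Two further objections hold. Single-visit comparisons may come from the Mann-Whitney test, which pools no variance across visits. And errors of at most about 2 points will seldom alter a judgement made against 16 to 20 points.

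**Conclusion.** The point holds in conditional form and is minor. If the model fitted is a random intercept with one residual variance, and if Quick DASH spread differs between visits, the model's single-visit intervals and tests do not have their nominal coverage and level. Under the unequal SD patterns tried, type I error ranged from about 4% to 13% at 2 weeks and from 0.3% to about 10% at 12 months; with equal SDs there is no error. All of these SDs are assumptions, so neither direction nor size can be stated as fact.

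The consequence is mainly for significance tests rather than for judging comparable function. The complication analysis by Fisher's test, the sample size and any single-visit Mann-Whitney test are untouched. Nothing was calculated for PRWE, grip strength or range of motion. Range of motion has three visits, from the end of immobilisation to 12 months, so the same reasoning applies to it in principle.

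**What to change.** In the Statistical analysis plan section, for Quick DASH and range of motion, replace the random-patient specification by a repeated-measures model with visit as a category, arm-by-visit terms, an unstructured covariance across visits and Kenward-Roger degrees of freedom. Name the fall-back in advance: visit-specific variances with robust standard errors if the unstructured model does not converge. State also whether the pre-injury score is a response or a covariate.

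This costs a sentence or two in the plan and no new data. The downside is more covariance parameters: five visits need 5 × 6 / 2 = 15, against about 100 randomised patients, which is why a fall-back is needed. With the pre-injury score as a covariate, four visits need 4 × 5 / 2 = 10, and range of motion with three visits needs 3 × 4 / 2 = 6. The change removes the dependence on equal visit variances whichever SD pattern the trial turns out to have.

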### Randomization

Randomization is executed by random drawing of sealed, opaque envelopes. According to the sample size calculation, 50 participants will be allocated to each group, hence 100 identical A5 envelopes have been sealed – each containing a folded note whereupon either “*operative”* or “*conservative”* is written. In order to assure similar timewise enrolment the following measures will be applied (Fig. 2). The 50 envelopes for operative treatment will be packed into stacks of 5 envelopes. The same will be done with the 50 envelopes for conservative treatment. One stack of each treatment arm will be mixed resulting in an equal chance to draw either treatment or intervention among the ten envelopes. The including health care personnel will draw one of the 10 envelopes and hence allocate the participant randomly to either treatment arm 1 or 2. When there are only three envelopes left, one stack of each group will be opened and mixed into the remaining. By this measure, the health care personnel cannot predict the allocated treatment based upon the order of previous mixed treatment allocation from the mixed pool of small envelopes.

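### For Quick DASH the plan does not say whether the Mann-Whitney test or the mixed model leads; only a model adjusted for the pre-injury score both uses that score and estimates the hypothesised mean difference

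*Protocol article*

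**What the plan says.** Under Statistical analysis plan, the article states: "That data will be analyzed using Fisher’s exact test and Mann Whitney U test". The same section adds that treatment effects over time will be assessed with "linear mixed effect models with patient treated as random factor", using a normal distribution and identity link for continuous measures. It lists no fixed effects and does not rank the two methods. The effect measure it names is an odds ratio.

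Under Primary outcomes, Quick DASH "will be used to assess the level of functionality prior to injury, after 2 weeks, 5 weeks, 6 months, and 12 months". For range of motion, the same section says: "The contralateral side will serve as a reference". Under Secondary outcomes, grip strength is recorded in both hands.

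Under Research hypothesis, comparable function is expressed as a mean difference in Quick DASH below 16–20 points. Under Randomization, the envelope scheme has no strata.

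**The concern.** The function claim depends on where the confidence interval for a mean difference lies relative to 16–20 points. One of the two named methods does not produce that quantity. A Mann-Whitney test compares rank distributions. It takes no covariate, and its p-value cannot show that a difference is smaller than a margin in points. An odds ratio, presumably meant for the complication rate, is not on the points scale either.

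The mixed model can supply the mean difference. But if the lead method is left open, it can be chosen after the results are seen. The way the pre-injury score enters the model also affects the width of the interval, and that is open too.

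**Working it through.** **The plan's own figure.** The article sizes the trial on complications only: "each group shall at least consist of 49 participants", and "50 participants will be allocated to each group". It gives a 20-point difference but no base rates. With an assumed 25% versus 5%, two-sided 5% alpha and 80% power, the pooled formula gives n = [1.96 × √(2 × 0.15 × 0.85) + 0.842 × √(0.25 × 0.75 + 0.05 × 0.95)]² / 0.20² = (0.990 + 0.408)² / 0.04 ≈ 48.8, so 49. Other base rates give other numbers (30% versus 10% gives 62). This has no bearing on the present point, because no continuous outcome was sized.

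**Inputs.**
- From the article: 50 per arm, two-sided 5% level, relevant difference 16–20 points.
- Assumed, because the article gives neither: follow-up SD 20 points (range 15–25), and correlation ρ between pre-injury and follow-up Quick DASH of 0.3–0.5.

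**Precision.** The 95% half-width is 1.96 × SD × √(2/50) × √(1 − ρ²), and √(2/50) = 0.2.

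| SD | no adjustment | ρ = 0.3 | ρ = 0.5 |
|---|---|---|---|
| 15 | 5.88 | 5.61 | 5.09 |
| 20 | 7.84 | 7.48 | 6.79 |
| 25 | 9.80 | 9.35 | 8.49 |

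The variance falls by ρ², which is 9% at ρ = 0.3 and 25% at ρ = 0.5. The equivalent sample size per arm is 50/(1 − ρ²), about 55 and 67. At ρ = 0.2 and SD 20 the half-width is still 7.68, so the gain is small if pre-injury scores predict little.

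**Chance imbalance.** An extreme (1.96 standard error) imbalance in the pre-injury score moves the unadjusted difference by ρ × 1.96 × SD × 0.2. At SD 20 this is 0.3 × 7.84 = 2.4 points or 0.5 × 7.84 = 3.9 points. The standard error already allows for such movement, so it is lost precision and not bias.

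**Effect on the conclusion.** For a true difference of 16 points, unadjusted power is Φ(16/4 − 1.96) = 97.9% at SD 20 and Φ(16/5 − 1.96) = 89.3% at SD 25. By symmetry, these are also the chances that the interval stays below 16 points when the true difference is zero. If the true difference were 5 points (assumed), the chance of staying below 16 is Φ(11/SE − 1.96):
- SD 20: SE 4.00, 3.82 and 3.46 for no adjustment, ρ = 0.3 and ρ = 0.5, giving about 79%, 82% and 89%.
- SD 25: SE 5.00 and 4.33 for no adjustment and ρ = 0.5, giving about 60% and 72%.

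**Why the form of the model matters.** Suppose the pre-injury score is the first visit in the model, with the arm means free at that visit. The arm-by-visit contrast against that visit is then a difference in change scores. With equal variances, its variance relative to follow-up alone is 2(1 − ρ): 1.4 at ρ = 0.3 and 1.0 at ρ = 0.5. Covariate adjustment gives 0.91 and 0.75. At SD 20 and ρ = 0.3 the half-widths are 7.84 × √1.4 ≈ 9.3 and 7.5 points. Both models fit the published sentence.

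**The case against.** A reader might infer that the trial analyses its continuous outcomes without the pre-injury score or the other wrist, although it collects both. The article does not support that. The mixed-model sentence names only the random factor. It does not even list arm or visit, which a model of treatment effects over time must contain, so it is plainly not a full specification. A condensed article may leave the covariate list to the full plan. The contralateral wrist has a stated role as reference for range of motion, and only its place in the analysis is unstated. No section plans to subtract one side from the other.

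A reader might also infer that chance imbalance in pre-injury function biases the comparison because randomisation is unstratified. It does not. Randomisation protects the unadjusted comparison, and its type I error is not inflated. Nor does the point reach every continuous outcome: PRWE and EQ5D have no pre-injury value in Table 1.

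It is also fair to say that the identity-link mixed model already estimates a mean difference, and that power for 16 points is about 89% or more over the assumed SD range, even unadjusted. A changed conclusion is therefore unlikely if the true difference is near zero.

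All of this stands, and it limits the point. It does not answer two things that the text does state or leave open: Mann-Whitney is a named method that cannot address the stated hypothesis, and nothing says that the mixed model takes precedence over it.

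**Conclusion.** The point holds in limited form and at low severity. For Quick DASH, the article names one method that estimates no mean difference and takes no pre-injury score, beside another that can do both, and does not say which leads. Whether the mixed model uses the pre-injury score cannot be told from the text. For range of motion, the role of the contralateral side is stated but its use in the model is not.

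The benefit of settling this is precision: at SD 20, a half-width of 7.5–6.8 instead of 7.8 points. It rests on an assumed SD and an assumed correlation of 0.3–0.5, and shrinks if the correlation is lower. An unadjusted randomised comparison would remain valid.

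**What to change.** State in the analysis plan that:

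- The linear mixed model is the lead analysis for Quick DASH, with arm, visit and arm-by-visit as fixed effects, pre-injury Quick DASH as a covariate, and patient as random factor. The follow-up visits are the outcome.
- The adjusted mean difference with 95% CI is reported at 6 and 12 months and read against the 16–20 point margin.
- For range of motion and grip, the contralateral value enters as a covariate. Table 1 schedules both measures only after randomisation, so the plan should add that treatment is assumed not to affect the uninjured side.
- Mann-Whitney is kept as a sensitivity analysis.
- PRWE and EQ5D are outside this change, as they have no pre-injury value.

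The cost is one or two sentences, with no new data and no more patients. The change should be made before the follow-up data are analysed by arm.
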